## Abstract

**Background:**

Exercise has consistently yielded short-term, positive effects on health outcomes in people with multiple sclerosis (MS). However, these effects have not been maintained in the long-term. Behaviour change interventions aim to promote long-term positive lifestyle change. This study, namely, “Step it Up” will compare the effect of an exercise plus Social Cognitive Theory (SCT)-based behaviour change intervention with an exercise plus control education intervention on walking mobility among people with MS.

**Methods/design:**

People with a diagnosis of MS who walk independently, score of 0–3 on the Patient Determined Disease Steps, who have not experienced an MS relapse or change in their MS medication in the last 12 weeks and who are physically inactive will be randomised to one of two study conditions. The experimental group will undergo a 10-week exercise plus SCT-based behavioural change intervention. The control group will undergo a 10-week exercise plus education intervention to control for contact. Participants will be assessed at weeks 1, 12, 24 and 36. The primary outcome will be walking mobility. Secondary outcomes will include: aerobic capacity, lower extremity muscle strength, participant adherence to the exercise programme, self-report exercise intensity, self-report enjoyment of exercise, exercise self-efficacy, outcome expectations for exercise, goal-setting for exercise, perceived benefits and barriers to exercise, perceptions of social support, physical and psychological impact of MS and fatigue. A qualitative evaluation of Step it Up will be completed among participants post-intervention.

**Discussion:**

This randomised controlled trial will examine the effectiveness of an exercise plus SCT-based behaviour change intervention on walking mobility among people with MS. To this end, Step it Up will serve to inform future directions of research and clinical practice with regard to sustainable exercise interventions for people with MS.

**Trial registration:**

ClinicalTrials.gov, NCT02301442

## Background

Multiple Sclerosis (MS) is a chronic, often progressive disease of the central nervous system that results in a variety of impairments that cause limitations in activities and participation restrictions. Mobility limitations are common [1,2] even in the early stages of the disease [3] and are of significant concern to people with MS [4,5]. Despite recent advances in pharmacological treatments, exercise therapy remains the cornerstone of the management of mobility limitations among people with MS.

There is an expanding body of evidence suggesting that exercise has positive effects on many of the impairments and subsequent activity limitations and restrictions in participation for people with MS. Systematic reviews and meta-analyses demonstrate that exercise has a positive effect on muscle strength [6,7], aerobic capacity [7], mobility [1], quality of life [8,9] and fatigue [10,11]. One recent review confirmed the safety of exercise for people with MS [12]. However, despite increasing evidence for the beneficial effects of physical activity (PA) and exercise, there is consistent evidence that people with MS are, in fact, less active than their healthy counterparts [13] and those with other health conditions [14]. Klaren et al. (2013) [15] demonstrated that 20% of PwMS in their study met public health guidelines for mild-to-vigorous PA when compared to 47% of the healthy controls. This is of concern given that reduced PA levels are associated with reduced quality of life [16], and increased risk of cardiovascular disease [17]. Indeed, a recent population study found that people with MS have a 2.4 fold increased risk of death due to cardiovascular disease than the general population [18] and this may be linked with physical inactivity [19].

A recent multi-centre block randomised controlled trial, which evaluated the effectiveness of community exercise interventions for people with MS who had minimal gait impairment, demonstrated significant benefits of exercise in the community [20]. Physiotherapist- and fitness- instructor- led interventions consisted of combined aerobic and strengthening training components. That exercise intervention resulted in significant improvements in the physical impact of MS, psychological impact of MS, impact of fatigue and walking endurance [20]. Of note, however, is that these improvements were not maintained over the longer term and the effect on the primary outcome measure (walking mobility) was no longer significant 12 weeks post-treatment [20]. Moreover, there was significant attrition with 50% loss to follow up at 24 weeks [20]. It is therefore imperative that future research interventions facilitate long-term adherence and positive changes in PA behaviour, in order to inform the implementation of sustainable exercise interventions for people with MS.

A behavioural outcome of paramount importance for optimised, long-term effectiveness of exercise programmes is exercise-adherence, particularly post-intervention PA behaviour [21].

Social Cognitive Theory (SCT) is one of the most widely-adopted theoretical frameworks for understanding and optimising PA and other health behaviours. Along these lines, researchers have developed a programme of work investigating a SCT-based behaviour change intervention. The intervention involves workshops that aim to enhance exercise self-efficacy and focus on the provision of information relative to PA participation based on the principles of SCT; namely outcome expectations, self-efficacy, impediments and goal setting. Previous research has demonstrated that individuals who completed the SCT-based intervention attended more exercise sessions than individuals in the standard care group [22]. Subsequent research using an online delivery [23] observed significant positive effects on PA as measured by the Godin Leisure Time Exercise Questionnaire that were subsequently replicated as a significant, large increase on accelerometer step counts [24]. Supplementing the programme with video coaching further increased PA and this change was maintained 12 weeks post-intervention [25].

Given the positive effects of these two separate but complementary areas of work it is probable that a combination of exercise and SCT-based behaviour change approaches could further improve and maintain health outcomes for people with MS. Step it Up will compare the effect of an exercise plus SCT-based behaviour change intervention with an exercise plus control education intervention on walking mobility among people with MS. Our hypothesis is that those in the exercise and SCT-based intervention will achieve significantly more improvement in walking mobility than the control group post-intervention (12 weeks) and that this improvement will be maintained at 24- and 36- week follow up.

## Methods/design

### Study design

This will be a multi-centre, double blind, randomised, controlled trial comparing an exercise plus SCT-based intervention with an exercise plus contact control education intervention. Outcomes measures will be administered at weeks 1, 12, 24 and 36. The study will be performed in agreement with the Declaration of Helsinki and is approved by the Health Service Executive Mid-West Research Ethics Committee, the Galway University Hospitals Clinical Research Ethics Committee and the University of Limerick, Faculty of Education and Health Sciences Research Ethics Committee.

### Sample size

It is assumed that the effect of the intervention yields an average improvement in 6 Minute Walk Test (6MWT) distance of 36 m with an estimated standard deviation of 48.2 m [26]. In order to have 80% power (at the 5% significance level) to detect such a difference in mean improvement in 6MWT over the study period between groups, a sample of size 62 randomised equally to two arms (i.e. 31 per arm) is needed. In order to account for potential drop out a sample of size 72 will be recruited.

### Recruitment and eligibility

The participants will be recruited using the social media, email and postal communications of the MS Society of Ireland. Additionally people with MS will be recruited via neurology clinics in three urban locations in the west and south of Ireland. People who are interested in taking part in the trial will be invited to contact the research team at the University of Limerick via phone or email, wherein they will be given an opportunity to ask questions about Step it Up. When contacted, the researcher will explain the study in detail. Potential participants will be screened for selection criteria over the telephone and participant information leaflet and informed consent forms via post or email will be sent to each potential participant. Inclusion criteria are: (1) physician-confirmed formal diagnosis of MS, (2) aged 18 years or more, (3) Patient Determined Disease Steps score of 0–3, (4) a sedentary lifestyle (<30 minutes of moderate to strenuous exercise one day or more per week over the last six months) and (5) willing to give written informed consent. Exclusion criteria are: (1) pregnancy, (2) MS relapse in the last 12 weeks and (3) changes to MS medication or steroid treatment in the last 12 weeks.

### Random allocation procedures

Participants will be randomly allocated individually to the exercise plus SCT-based intervention or the exercise plus contact control education intervention. The allocation sequence will be concealed from all study personnel until after data collection is complete. All participants will be informed that we are evaluating the effect of combining exercise and education, and as such will be blind to their group allocation.

### Intervention procedures

#### Exercise plus contact control education intervention

The control group will receive an exercise and a didactic control education component. The exercise intervention will be common to both groups, will include aerobic and strengthening components and will be delivered by physiotherapists who are trained in the delivery of this standardised exercise intervention. The aim of the exercise component is to progressively increase the intensity of both aerobic and strengthening activities to enable the participants to reach the recently published MS exercise guidelines [7]. The aerobic activity will be walking, the intensity of which will be monitored using step rate measured using the Yamax digiwalker pedometer* (which will be provided to all participants) and an exercise log to document duration of walking exercise and number of steps taken. It is widely accepted that 100 steps per minute equates to three MET or moderate intensity PA among various clinical populations [27,28]. Similar values have been established for people with MS where the mean step-rate threshold at three METs for mean heights was 99 for people with MS who had minimal walking impairment and 96 for those with MS who had mild-moderate walking impairment [29]. Thus the target walking exercise intensity for both groups in the current study will be a rate of 100 steps per minute. Participants will begin with 10 minutes of walking twice weekly at a rate of 100 steps/minute and increase incrementally in 5 minute intervals over 5 weeks until they reach the guideline of 30 minutes twice weekly [7].

The strengthening programme is based on a community-based exercise programme that has been evaluated previously [20] and will consist of ten exercises targeting major muscle groups for the upper and lower extremities using elastic resistance band. The intensity and duration of the strengthening component of the intervention will be progressed by increasing the number of repetitions and sets and changing the resistance of the elastic resistance band used for each strengthening exercise. Participants will begin with one set of 10–15 repetitions and gradually increase the number of sets, repetitions and level of resistance until they meet the target of two sets of each exercise twice weekly with sufficient resistance that they are failing on the 12th repetition. Over the 10-week programme participants will attend the group exercise class on six occasions, supplemented with a telephone coaching call in the weeks without classes (intervention weeks 4, 6, 7 and 9). These telephone calls will consist of direct questions about the frequency, intensity, type and duration of exercise they have completed and whether they have experienced any adverse events or relapses. Of note, these telephone calls will also be conducted at weeks 16, 20 and 36, after the 10-week intervention has been completed. After each of the group exercise classes the control group will receive an education session about topics unrelated to PA behaviour, e.g. diet, vitamin D, sleep, temperature and hydration, and immunisations and vaccinations.

#### Exercise plus SCT-based intervention

The exercise plus SCT-based intervention group will receive the same exercise intervention as the control group (as described in the previous section).This group will also receive a behaviour change intervention based on the principles of SCT. The SCT-based education sessions will be delivered after each exercise session by physiotherapists who are trained in this area and will incorporate the principle elements of SCT including self-efficacy, outcome expectations, impediments and goal-setting. Session 1 will consist of a discussion on the benefits of exercise for persons with MS, instructions for beginning an exercise program, education on outcome expectations (physical, social, self-evaluative and mental outcome expectations) of the Step it Up intervention and instructions on effective self-monitoring of one’s behaviour (use of exercise logs and pedometers). Session 2 will include group discussion and physiotherapy-led guidance on setting specific, measureable, adjustable, action-oriented, realistic and time-based exercise and PA goals. Participants will also complete group-based written assignments and document their exercise goals during this session. Session 3 will focus on the concept of self-efficacy, with emphasis on the sources of self-efficacy, namely: mastery accomplishments, social modelling, social persuasion and the interpretation of physiological states. Session 4 will consist of discussion and documentation of the barriers and facilitators of exercise (environmental, social, health and cognitive and behavioural). Session 5 will focus on the concept of long-term maintenance of a physically-active lifestyle. The last education session will involve a celebratory ceremony for the participants to commend them on their successful completion of the Step it Up programme. Beyond providing presentation notes, individual reflection and written exercises, group discussion on each of the principles of SCT, and providing on-going feedback on all aspects of PA behaviour, the program will include video files of people with MS discussing PA behaviour and their experiences of initiating and maintaining a physically-active lifestyle. The use of video files of people with MS is grounded in a central tenet of SCT- the promotion of self-efficacy via social modelling and social persuasion. On the weeks when the participants do not attend group sessions, they will receive a telephone coaching call from the physiotherapist. These coaching calls will consist of guided conversations that consider the components of SCT delivered in the previous session and a revision of other components. Of note, participants will also receive telephone coaching calls from the physiotherapists at weeks 16, 20 and 36 (after the 10-week programme has been completed) in order to revise the topics covered during the Step it Up programme and to act as a support for long-term maintenance of a physically-active lifestyle.

#### Ensuring the fidelity of the interventions

A manual of operating procedures will be provided to the physiotherapists and incorporated into training for the physiotherapists and provided to them for their use throughout their delivery of the Step it Up programme. The physiotherapists’ adherence to the Step it Up intervention protocol will be verified using ad-hoc video analysis of the intervention programme. Fidelity of the intervention dose will be further monitored by recording participant attendance for each session and participant exercise completion and intensity of exercise using exercise log books throughout the 10-week intervention.

#### Screening measure

Potential participants will be screened for eligibility for this study using the PDDS scale [31]. The PDDS scale contains a single item for measuring self-reported neurological impairment on an ordinal level from zero (Normal) to eight (Bedridden). Scores from the PDDS are linearly and strongly related with physician-administered Expanded Disability Status Scale (EDSS) scores [31].

#### Primary outcome

Consistent with the finding that people with MS report mobility limitations as their greatest concern [5], the primary outcome will be walking mobility. This will be measured by the Six Minute Walk Test (6MWT), Timed Up and Go test (TUG) and the Multiple Sclerosis Walking Scale-12 (MSWS-12) in order to capture walking endurance, walking speed and participant-reported limitations in walking.

The 6MWT will involve the participants being instructed to walk for six minutes as quickly and safely as possible [33] and the distance (m) covered will be recorded. The 6MWT has demonstrated excellent test-retest reliability and concurrent validity among people with mild to moderate MS [33].

For the TUG, the participants will be instructed to stand up from a chair, walk 3 m, then turn around walk back to the chair and sit down, as quickly and safely as possible. The participants’ performance will be timed and the mean score of three performances of the TUG will be used in analysis. TUG-cognitive involves adding a cognitive task (subtracting three from a random number between 20 and 100) while performing the TUG. Previous research demonstrates excellent test-retest reliability for people with mild MS (EDSS: 0–4) [34].

The MSWS-12 will be used to measure participants’ self-reported walking limitations due to MS during the previous two weeks. All items are measured on a likert scale ranging from 1 (not at all) to 5 (extremely). Psychometric testing of the MSWS-12 has demonstrated that it has excellent internal consistency [35,36], test-retest reliability [37] and concurrent validity [38].

#### Secondary outcomes

The 5 times sit to stand test [39] will be used to measure lower extremity muscle strength. The participants will be instructed to stand up and sit down as quickly as possible when rising from a chair. It has demonstrated excellent construct validity among people with MS [33]. The 5 times sit to stand test has also demonstrated moderate to excellent concurrent validity among people with MS who had mild to moderate disability [40].

Aerobic capacity will be measured among participants using the Modified Canadian Aerobic Fitness Test [41] (mCAFT). The mCAFT is a graded step test and can predict VO_2peak_ using a published regression equation for people with MS [42].

The Hospital Anxiety and Depression Scale (HADS) [43] is a 14-item self-report scale and will be used to measure anxiety and depression among participants. The HADS has been validated among people with MS, demonstrating acceptable sensitivity (90% and 89% for the depression subscale) and specificity (87% and 81% for the anxiety subscale) [44].

The Symbol Digit Modalities Test (SDMT) [45] will be used to measure processing speed. Participants will be presented with a series of nine geometric symbols, each paired with a different single digit number in a key at the top of the page. Participants will be instructed to provide the digit associated with each corresponding symbol and the score shall be the number correctly completed in 90 seconds. The SDMT is a commonly-used, validated assessment of cognitive function in individuals with MS [46].

PA will be measured using the Godin Leisure-Time Exercise Questionnaire (GLTEQ) [47] and the short-form of the International Physical Activity Questionnaire (IPAQ) [48]. Evidence for the validity of these measures in people with MS has been reported [49-51]. The GLTEQ is a self-administered assessment that has three items that measure the frequency of strenuous, moderate, and mild physical activities for periods of more than 15 min during a person’s free time over the previous week. The short-form of the IPAQ was designed for population surveillance of PA among adults and measures the frequency and duration of vigorous-intensity activities, moderate-intensity activities, walking and sitting during a 7-day period.

Additionally, the SenseWear Arm band (SWA) will be used as an objective estimate of PA using both mean daily step count and mean daily energy expenditure estimates over a 7-day period. The acceptable criterion validity of the mean daily energy expenditure (kilocalorie estimates) over a 7-day period of the SWA has been demonstrated among people with mild disability with MS [52].

Adherence to the exercise programme will be documented throughout the 10-week intervention via self-report exercise logs. These exercise logs will capture information regarding participant attendance at the exercise classes. In relation to the strengthening component of the exercise programme, the number of sets, repetitions and colour of resistance band used will be recorded for each exercise during each exercise session. Additionally, the duration of each walking exercise session and pedometer-measured step count will be recorded in the exercise logs. The logs will also record participants’ reported enjoyment of each exercise session using a likert scale ranging from one (not at all) to seven (very much) and their perceived rate of exertion during each exercise session using a likert scale ranging from 6 (no exertion at all) to 20 (maximal exertion) [53].

Five questionnaires will be implemented to measure SCT domains. These include the Exercise Self-Efficacy Scale (EXSE), Exercise Goal Setting (EGS) scale [54], Multidimensional Outcomes Expectations for Exercise Scale (MOEES) [55], the Social Provisions Scale (SPS) [56] and an exercise benefits and barriers questionnaire. These questionnaires have been validated and have been used in previous research on PA [23,57,58].

The Multiple Sclerosis Impact Scale 29 (MSIS-29) [59] is a measure of the physical and psychological impact of MS from the patient’s perspective. Excellent internal consistency for the physical and psychological subscales, respectively, and moderate to excellent concurrent validity for the physical and psychological subscales, respectively have been reported for the MSIS-29 [60].

The Modified Fatigue Impact Scale (MFIS) is a 21-item self-report questionnaire and will measure the impact of fatigue on physical, cognitive and psychosocial aspects functioning among participants. Excellent test-retest reliability [61], internal consistency [62] and concurrent validity [61] has been reported in MS populations.

#### Statistical analysis

Suitable numerical statistics and graphical summaries will be used to describe characteristics of the sample at baseline and to assess the validity of any distributional assumptions needed for the formal analysis. The flow of trial participants and the level of missing data for all outcomes will be documented and an analysis into the cause of missingness (if present) will be conducted. All losses to follow-up and dropouts will be accounted, and where possible, reasons documented. The primary analysis will compare differences in the primary response variable, namely the difference in mean steps between the two treatment arms across the 12 week time period. Several analyses will be performed to compare the change in the primary response variable across time and between groups while adjusting for baseline as appropriate. These will include linear mixed models for a continuous response with different covariance structures compared in order to best model the correlation structure within subjects across time. All tests of significance will be two-sided and conducted at an alpha = 0.05 level of statistical significance. A further analysis will be performed to compare the estimated effect of the intervention when imputing values for all missing data in order to investigate the assumptions relating to missingness, and the effect, if any, on the overall conclusion. Multiple imputation will be performed using a Predictive Model Based Method using chained equations where each missing value is replaced by 20 imputed values. The results of each ‘complete’ model (i.e. with imputed values) will be averaged using the Barnard-Rubin adjustment method.

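### The primary analysis is defined on mean steps, but the declared primary outcome is walking mobility and the sample size rests on 6MWT distance, so the stated power does not cover the primary test as written

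*Protocol article*

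**What the plan says.** Four parts of the protocol article bear on this point.

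- **Primary outcome.** The concept is fixed first: "the primary outcome will be walking mobility". The instruments follow: "This will be measured by the Six Minute Walk Test (6MWT), Timed Up and Go test (TUG) and the Multiple Sclerosis Walking Scale-12 (MSWS-12". For the 6MWT, "the distance (m) covered will be recorded". TUG is a time, and MSWS-12 is a self-report scale.
- **Sample size.** The assumed effect is an improvement in "6 Minute Walk Test (6MWT) distance of 36 m with an estimated standard deviation of 48.2 m", and the stated aim is to "detect such a difference in mean improvement in 6MWT over the study period between groups", with 80% power at the 5% level, 31 per arm, and 72 recruited to allow for dropout.
- **Statistical analysis.** The primary analysis compares "the primary response variable, namely the difference in mean steps between the two treatment arms across the 12 week time period". The mixed models and other analyses that follow are also described as acting on the primary response variable. All tests are two-sided at 0.05.
- **Secondary outcomes.** Steps appear here twice: from the SenseWear armband as an "objective estimate of PA using both mean daily step count and mean daily energy expenditure estimates over a 7-day period", and in the adherence records, where "the duration of each walking exercise session and pedometer-measured step count will be recorded in the exercise logs".

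The Abstract, the closing hypothesis of the Background, and the Discussion all state the aim as walking mobility. The hypothesis sets the between-arm comparison at 12 weeks, with maintenance at 24 and 36 weeks.

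**The concern.** The primary analysis names a variable that is not among the declared primary measures and was not used to size the trial. An analyst who follows the Statistical analysis section literally would run the decisive test on a physical activity measure that the article itself classes as secondary. That section does not say which of the two step sources is meant.

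Two things are at stake. First, the 80% power claim belongs to 6MWT distance and cannot be carried over to steps. Second, the comparison that the trial was sized for has no designated primary test. Steps describe how much a person walks; the 6MWT describes walking endurance. The first can differ between arms without the second doing so, so a result on steps would not by itself answer the stated hypothesis.

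**Working it through.** **Step 1. Compare the sections.**

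| Section | Variable | Unit | Time |
|---|---|---|---|
| Background (hypothesis) | Walking mobility | not given | 12 weeks; maintained at 24 and 36 |
| Sample size | 6MWT improvement | metres | study period, no week given |
| Primary outcome | 6MWT, TUG, MSWS-12 | metres, time, scale score | not given |
| Statistical analysis | Mean steps | steps | across 12 weeks |
| Secondary outcomes | Armband daily steps; pedometer steps per session | steps | 7-day wear; logs over the 10-week programme |

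Only the Statistical analysis section makes steps primary. The pedometer logs cover 10 weeks, so they do not match a 12-week window.

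**Step 2. Reproduce the plan's sample size.** Inputs from the Sample size section: difference 36 m, SD 48.2 m, power 80%, 5% level, equal allocation. Two-sided testing comes from the Statistical analysis section.

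- Standardised effect: d = 36 / 48.2 = 0.747.
- Normal approximation: n per arm = 2 × (1.960 + 0.842)² / 0.747² = 28.1, rounded up to 29 (58 in total).
- Two-sample t-test: n = 29.13, rounded up to 30 per arm (60 in total), within 2 of the stated 62.
- Dividing the t-test figure by the Mann-Whitney efficiency: 29.1 / 0.955 = 30.5, rounded up to 31 per arm (62 in total), an exact match. The article does not say that this adjustment was used.
- One-sided testing would give 23 per arm, which does not fit.

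The stated size is therefore consistent with 6MWT distance as its sole basis.

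**Step 3. Power at 31 per arm for the 6MWT.** Normal approximation: 0.747 × √(31/2) − 1.960 = 0.98, which gives 83.7%. The t-test gives 82.5%.

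**Step 4. Power at 31 per arm for steps.** The article gives no step difference and no SD, so this cannot be calculated. Purely as assumed values of d (t-test, two-sided 0.05):

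| Assumed d for steps | Power |
|---|---|
| 0.2 | 12% |
| 0.3 | 21% |
| 0.4 | 34% |
| 0.5 | 49% |
| 0.6 | 64% |
| 0.747 | 82% |

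A d of 0.72 would be needed for 80% power. Whether steps would reach it is unknown from the document.

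**The case against.** The strongest reply is that this is a drafting slip. Every other statement of the aim, from Abstract to Discussion, says walking mobility, so a careful reader would notice the mismatch and could guess that the 6MWT was intended. That is plausible, but it does not remove the problem. Step counts really are collected, so the sentence can be carried out as it stands, and nothing in the article corrects it. Nor is this a detail left to a statistical analysis plan: the article itself names a primary response variable, and the name conflicts with its own outcome and sample size sections.

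A reader might infer more than the document supports:

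- **That the time frames contradict each other (12 versus 36 weeks).** The Sample size section gives no number of weeks. Its phrase can be read consistently with the week-12 hypothesis. It is ambiguous, not contradictory.
- **That the primary test is on armband steps.** The pedometer is an equally possible source, and the article does not choose.
- **That steps favour the experimental arm because of the pedometers.** All participants receive a pedometer, and both arms have the same step-rate target. What does differ is the education: the experimental arm is taught self-monitoring with logs and pedometers, while control education is unrelated to activity behaviour. That shows the arms could differ on steps, not that they will.
- **That a steps result would be passed off as a mobility result, or the endpoint chosen after the data are seen.** The mismatch leaves that possible, but nothing in the article indicates intent, and its consistent statement of the aim would expose it.
- **That the trial is too small.** The sample size arithmetic is sound for the 6MWT.

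**Conclusion.** The point stands in this form: the primary response variable in the Statistical analysis section contradicts the Primary outcome and Sample size sections. As written, the primary test falls on a measure that the article lists as secondary. The power for that test is undefined, while the roughly 82% available at 31 evaluable per arm belongs to a 6MWT comparison with no designated primary test. The 82% rests on the article's own 36 m and 48.2 m and a two-sided two-sample t-test. The 12% to 82% range for steps rests on assumed effect sizes and shows only how much depends on an unstated input. Because the trial's main inference is affected and the correction is textual, it should be made before analysis.

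**What to change.** 1. **Statistical analysis.** Replace the reference to mean steps with the between-arm difference in 6MWT distance (m) at week 12, adjusted for baseline 6MWT. This matches the Sample size section and the week-12 hypothesis. Weeks 24 and 36 then serve the maintenance part of the hypothesis.
2. **Primary outcome.** Name the 6MWT as the single primary measure, and state that TUG and MSWS-12 are supporting or secondary measures of walking mobility. Without this edit, three primary measures would still face one primary test. If the sponsor prefers to keep all three as primary, state how alpha is shared.
3. **Secondary outcomes.** Keep step counts here.
4. **Sample size.** Clarify the period as baseline to week 12.

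If steps are truly intended as primary, the article should justify this, name the device and give a power calculation for steps.

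**Cost.** Items 1 to 4 change wording only. The sample size stands, and no extra data or participants are needed. The one loss is that TUG and MSWS-12 give up co-primary status. Keeping all three could cost more: with an equal Bonferroni split (0.05/3), the t-test needs 39 per arm for the same 36 m and 48.2 m, or 78 evaluable, against 72 to be recruited.
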